**Nociceptive procedures**
Chest tube removalDrain removalMouth, endotracheal, or tracheal suctioningArterial line insertionPeripheral intravenous line insertionSubcutaneous injectionWound careBed turning or repositioning
**Nonnociceptive procedures**
Soft touch of the patient’s armNoninvasive blood pressure cuff inflation (NIBP)

**Table 1 table1:** Assessment time points and pain variables to be measured in each group (A, B, and C).

Measure	Nonnociceptive procedures					Nociceptive procedure 1				Nociceptive procedure 2				Analgesic^a^	
	Pre	Soft touch	Cuff inflation	Post	Pre		During	Post	Pre		During	Post	Pre		Post
NOL^b^	A^c^, B^d^, C^e^	A, B, C	A, B, C	A, B, C	A, B, C		A, B, C	A, B, C	A, B, C		A, B, C	A, B, C	A, B, C		A, B, C
Behaviors	A, B	A, B	A, B	A, B, C	A, B		A, B	A, B	A, B		A, B	A, B	A, B		A, B
Pain level	A	A	A	A	A		A	A	A		A	A	A		A

^a^Administration of an analgesic as required by the patient’s condition.

^b^NOL: Nociception Level Index.

^c^Group A: Patients are able to communicate their self-report of pain and can exhibit behaviors.

^d^Group B: Patients are unable to communicate their self-report of pain but can exhibit behaviors.

^e^Group C: Patients who cannot communicate their self-report of pain or exhibit behaviors.

### Variables and Measurement Tools

#### Primary Measure: The Nociception Level (NOL) Index–All Groups (A, B, and C)

The Pain Monitoring Device-200 (PMD-200; Medasense Biometrics Ltd; Figure 1) is used in this study. PMD-200 offers the multiparametric NOL index (0-100) and was approved by Health Canada for clinical use in September 2017. The NOL captures several physiological parameters simultaneously through a finger probe and disposable sensor, which includes 4 small sensors, sampled 50-500 Hz: (1) accelerometer, (2) photoplethysmograph, (3) galvanic skin response, and (4) peripheral temperature. From these 4 sensors, the following physiological parameters are extracted: heart rate, heart rate variability, photoplethysmography pulse wave amplitude, skin conductance level, number of skin conductance fluctuations, skin temperature, and their time derivatives. All these parameters are integrated and analyzed simultaneously using a Random Forest machine learning model approach to provide the NOL index, which can range from 0 to 100 [17]. A NOL cutoff value >25 for the detection of self-reported pain was found in our pilot study with ICU cardiac surgery patients [27].

**Figure 1 figure1:**
[figure not shown]
Nociception Level (NOL) index.

The PMD-200 device allows the documentation of each event (ie, beginning and end time of rest and procedure assessment) or any contextual information (eg, interruption during a procedure), which is facilitated with the use of a wireless keypad. All NOL data are electronically collected every 5 seconds by the PMD-200 monitor.

#### Reference Standard Measure of Pain–Group A

The Faces Pain Thermometer (FPT) was selected to measure pain intensity as it can accommodate adult patients of various ages. It consists of an enlarged visual thermometer including 6 faces with a numeric rating scale scoring from 0=“no pain” to 10=“worst possible pain” (Figure 2). The validity and reliability (test-retest) of the tool were established in ICU patients [35]. The FPT was used in many previous validation studies led by the primary investigator [13,34,36] and pilot NOL studies [26,27].

**Figure 2 figure2:**
[figure not shown]
The 0-10 Faces Pain Thermometer (FPT)[35].

#### Alternative Reference Standard Measure of Pain–Groups A and B

The Critical-Care Pain Observation Tool (CPOT) [13] was selected for behavioral pain assessment in critically ill adults. The CPOT was used in our NOL pilot studies [26,27], and it is 1 of the 2 behavioral scales suggested as alternative reference standard measures of pain by the Society of Critical Care Medicine [14] and has been implemented in clinical practice in the 3 study ICUs. The CPOT includes 4 behavioral items: (1) facial expressions, (2) body movements, (3) muscle tension, and (4) compliance with the ventilator (for mechanically ventilated patients) or vocalization (for nonintubated patients). Each item is scored from 0-2, and the total score can range from 0-8. The CPOT has been validated in 47 studies with more than 3900 ICU patients with surgical, trauma, and medical diagnoses from various countries [34]. Consistent findings of good interrater reliability (interclass correlation coefficient [ICC] >0.60 between research staff and ICU nurses) and ability to discriminate between various nociceptive and nonnociceptive procedures were found across studies. Criterion validation of the CPOT was also supported by positive correlations (*r*>0.40) with ICU patients’ self-reported pain intensity [34]. A CPOT score >2 was found to adequately identify patients with self-reported pain (AUC>0.80) [34,36].

The research staff of all sites have been trained to use the CPOT using a standardized training session previously described [37]. Briefly, this 60-minute training session covers the description of the CPOT content and its scoring process. Patient videos are viewed to practice scoring with the tool with the goal of reaching consistent CPOT scores between raters within a total score difference of no more than 1 point.

#### Demographic and Clinical Information for ICU Patient Participants

Demographic information (eg, age, sex, gender, and ethnicity) is collected from the patient or their representative. Information related to the patient’s clinical condition (ie, ICU admission diagnosis, mechanical ventilation, the severity of illness [Acute Physiology and Chronic Health Evaluation; APACHE II] [38], level of consciousness [GCS] [30], sedation level [RASS] [31], delirium screening with the Confusion Assessment Method-ICU [39] or Intensive Care Delirium Screening Checklist [40], according to the respective tool used at each site), as well as medication information (ie, morphine equivalent doses [41] received within 4 hours before and during the entire data collection, sedative agents, vasopressors, and use of opioids before ICU admission) is extracted from the medical records by the research staff. The following clinical information is collected at the time of obtaining consent and performing data collection: mechanical ventilation status, GCS score, RASS score, and delirium screening.

### Sample Size Calculation

The primary objective is to validate the NOL using pain standard criteria (ie, self-report and CPOT scores). Therefore, ROC is considered our primary analysis and guides the sample size calculation for Group A and Group B. Power calculations were based on our pilot findings [26,27] and results from previous ICU studies considering a clinically acceptable AUC of 0.75 [42] (using a null hypothesis of AUC=0.50) with a power of 80% and an adjusted α of .025 (2 ROC curves for each procedure in each group). For Group A in whom the self-report of pain is obtained and using a ratio of 2:1 in pain:no pain cases according to self-reported pain intensity scores of <4 and >4, a sample of 54 patients is required. For Group B in whom only the CPOT scores are available and using a ratio of 1.5:1 in pain:no pain cases according to CPOT scores of <2 (no pain) and >2 (pain), a sample of 50 patients is necessary. For Group C (unable to self-report and express behaviors), we will not be able to use any pain standard criterion. Therefore, our main objective is to test whether the NOL can discriminate between a nociceptive procedure and a nonnociceptive procedure. In order to detect a minimal mean increase of 10 in the NOL value during the nociceptive procedure (with a standard deviation of 10 as found in our pilot findings), a minimal sample size of 13 patients is required to run paired *t* tests with a power of 80% and an α of .01 (to account for multiple test comparisons). Considering an attrition rate of 25% (data collection was completed in 73% of consenting patients in our pilot work), recruitment targets include 68 patients in Group A, 62 patients in Group B, and 16 in Group C for a total of 146 ICU patients. Power calculations were performed by a statistician using Power and Precision 4 (Biostat Inc).

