Although the validity of the NOL is supported in anesthesia, its use in the ICU is new. To our knowledge, we are the first research team to have pilot-tested the use of the NOL for nociception and pain assessment in the ICU. We conducted 2 pilot studies in 15 mechanically ventilated [26] and 54 cardiac surgery ICU patients [27] able to self-report their pain. In both studies, discriminative validation of the NOL was supported with higher index values during nociceptive procedures (ie, chest tube removal, endotracheal suctioning) compared with rest and a nonnociceptive procedure (ie, noninvasive blood pressure [NIBP] using cuff inflation). The NOL values were positively associated with self-reported pain and CPOT scores during nociceptive procedures, providing initial evidence of criterion validation with pain standard criteria [26,27]. Also, a NOL cutoff >25 was found to adequately classify patients with moderate to severe self-reported pain intensity (>4/10) [27]. However, these pilot validation studies of the NOL were limited to 2 nociceptive procedures as part of standard care and were solely conducted in ICU patients who were able to self-report. Further validation of the NOL during various standard care procedures in critically ill adults with different levels of consciousness or sedation and in response to analgesic treatment is necessary to confirm its validity for the assessment of nociception and related pain in the ICU.

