### Study Rationale, Goal, Objectives, and Research Hypotheses

An instrument can only be shown as valid for a specific purpose in a given population and context [28]. The NOL index was initially developed and validated for nociception monitoring and related pain in anesthetized patients [17,19-25]. Therefore, validating its use for nociception (primary purpose) and pain assessment (related purpose) in critically ill adults admitted to the ICU (different population and context of care) is necessary. Inspired by our pilot work, strategies for this larger validation study include: (1) criterion validation (ie, NOL’s ability to detect pain according to pain standard criteria) and (2) discriminative validation (ie, NOL’s ability to discriminate between nonnociceptive and nociceptive procedures) [28]. Considering that reliability is a necessary condition for validity [28], test-retest reliability of the NOL’s ability to generate consistent values in similar conditions (eg, at rest) will also be examined.

Research Question: Is the NOL a valid method for the assessment of nociception and pain in critically ill adults in the ICU context?

In order to answer this research question, specific validation objectives are to examine the NOL’s ability to:

Detect pain in ICU patients able or not to self-report using appropriate pain standard criteria (ie, criterion validation);Discriminate between nonnociceptive and nociceptive procedures part of standard care as well as before and after the administration of a breakthrough opioid dose (ie, discriminative validation);Generate consistent values in similar conditions (ie, pre- and post-nonnociceptive and nociceptive procedures) when ICU patients are at rest.

Our research hypotheses to be tested include:

H1. The NOL index adequately classifies ICU patients with pain based on either their self-reported pain intensity or CPOT scores.

H2. The NOL index produces higher values during nociceptive procedures compared to nonnociceptive procedures and lower values post- versus preopioid administration.

H3. The NOL index generates consistent values pre- and post-nonnociceptive and nociceptive procedures when ICU patients are at rest.

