Discriminative validation (objective 2) is our main objective to test in Group C, and paired *t* tests comparing the NOL values of each nociceptive procedure with the nonnociceptive procedure will be obtained. Generalized linear mixed model for repeated measures will allow us to compare the NOL index values across time points (pre, during, and post), procedures (nonnociceptive vs nociceptive), and their interaction in each group (A, B, and C). The generalized linear mixed model technique incorporates the full-information maximum likelihood procedure, which allows parameter estimation for missing data [47]. NOL values are expected to be significantly higher during nociceptive procedures in all 3 groups. Covariates (eg, sex, gender, morphine equivalent doses, opioid use before ICU admission) may be added if appropriate. Finally, NOL data obtained at pre- and postadministration of an opioid dose will be tested separately using paired *t* tests as not all patients will be candidates for these assessments.

For test-retest reliability (objective 3), paired *t* tests will be performed between pre and post-nonnociceptive and nociceptive procedures in all 3 groups. Nonsignificant paired *t* tests are expected to support the stability of NOL values when the patients are at rest.

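### Group C: 16 recruits at 25% attrition leave 12, below the plan's own minimum of 13, and the unstated sidedness puts power at about 76% or 64% rather than 80%

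*Protocol article*

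**What the plan says.** Under Sample Size Calculation, Group C is sized separately because no pain criterion is available for these patients. The target effect is worded as an increase: "In order to detect a minimal mean increase of 10 in the NOL value during the nociceptive procedure". The spread is given "with a standard deviation of 10 as found in our pilot findings", without saying whether it is the SD of paired differences or of single NOL values. The significance level is "an α of .01 (to account for multiple test comparisons". From these inputs the article concludes that "a minimal sample size of 13 patients is required to run paired *t* tests with a power of 80% and an α of .01".

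The same paragraph then assumes 25% attrition, citing completion in 73% of consenting patients in the pilot work, and sets the Group C target at 16.

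Under Data Analysis, the Group C tests are paired *t* "tests comparing the NOL values of each nociceptive procedure with the nonnociceptive procedure will be obtained". Neither section says whether they are one-sided or two-sided. The second research hypothesis is directional: "The NOL index produces higher values during nociceptive procedures compared to nonnociceptive procedures".

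**The concern.** Two things in this calculation do not close. First, an α of .01 with no sidedness can mean two different tests, and 13 patients give 80% power for only one of them if the SD is that of the paired differences. An analyst who runs the default two-sided paired *t* test at .01 would have less power than the article states. Second, the attrition allowance is meant to leave at least 13 completers, and 16 recruits at 25% attrition do not.

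Discrimination between procedures is the article's main objective in Group C, the patients for whom neither self-report nor behaviour can be used. If power is believed to be 80% when it is nearer 64% or 76%, a nonsignificant result could be taken as stronger evidence against the device than it is.

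**Working it through.** **Inputs** (all from Sample Size Calculation): mean paired difference 10; SD 10; α = .01; target power 80%; stated minimum 13; attrition 25%; recruitment target 16.

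**Assumption:** SD 10 is the SD of the paired differences, so d = 10/10 = 1.

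**Formula:** a paired *t* test on n patients has n − 1 degrees of freedom and noncentrality d√n. Power is the probability that a noncentral *t* variable exceeds the critical value (for the two-sided test, in either direction).

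**Step 1: reproduce the stated 13.**
- One-sided α = .01, n = 13: critical value 2.681, noncentrality √13 = 3.606, power 80.6%. At n = 12 power is 75.9%, so 13 is the smallest n that reaches 80%. The figure reproduces.
- Two-sided α = .01, n = 13: critical value 3.055, same noncentrality, power 70.1%. The figure does not reproduce.

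**Step 2: power by number of completers (d = 1, α = .01).**

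| Completers | One-sided | Two-sided |
|---|---|---|
| 12 | 75.9% | 64.2% |
| 13 | 80.6% | 70.1% |
| 14 | 84.5% | 75.2% |
| 15 | 87.7% | 79.7% |
| 16 | 90.3% | 83.5% |

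A two-sided test therefore needs 16 completers; 15 falls just short.

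**Step 3: attrition.**
- Expected completers: 16 × (1 − 0.25) = 12. At the pilot completion rate: 16 × 0.73 = 11.7.
- Where 16 seems to come from: 13 × 1.25 = 16.25. The other groups show the same pattern: 54 × 1.25 = 67.5 (target 68) and 50 × 1.25 = 62.5 (target 62).
- What 25% attrition requires: 13/0.75 = 17.3, so 18 recruits. For 16 completers: 16/0.75 = 21.3, so 22.

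**Step 4: sensitivity to the SD assumption.** If 10 is the SD of single values, the SD of the differences is 10√(2(1 − ρ)), where ρ is the within-patient correlation. The article gives no ρ, so the values below are an assumed range (α = .01).

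| ρ | SD of differences | n = 12, one-sided / two-sided | n = 13, one-sided / two-sided |
|---|---|---|---|
| 0 | 14.1 | 43.0% / 31.3% | 47.5% / 35.5% |
| 0.5 | 10.0 | 75.9% / 64.2% | 80.6% / 70.1% |
| 0.6 | 8.9 | 85.4% / 75.9% | 89.1% / 81.2% |
| 0.7 | 7.7 | 94.2% / 88.5% | 96.2% / 92.1% |

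Under this alternative, power could be much lower or higher than stated. The attrition result in step 3 does not depend on it.

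**The case against.** The strongest reply is that 13 is not an arithmetic error. A reader might infer that the test is two-sided and that the article claims 80% where the truth is 70%. The article does not support that. It nowhere says two-sided, it sizes for an increase, its hypothesis predicts higher values, and 13 is exactly the smallest n for a one-sided test at .01. This objection stands: 70.1% is what a two-sided analysis would have, not a refutation of the stated figure.

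One might answer that the Group A and B sizes look two-sided, so Group C should be too. That is circumstantial. Those sizes fit a two-sided test only under one choice of ROC variance formula, the article does not name the formula, and the tests are of a different kind.

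The SD is also ambiguous. With an SD of single values and a correlation near 0.6, 13 would serve a two-sided test as well (81.2%). So the statement that 13 fits only a one-sided test holds under the paired-difference reading alone.

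A reader might also infer that this is the only confirmatory test in Group C. The article also plans a mixed model for repeated measures there, which uses more time points, and it names the ROC analysis in Groups A and B as primary. Finally, the pilots were "solely conducted in ICU patients who were able to self-report", so the SD is carried over to a different kind of patient. The article discloses its source, and nothing in it allows the effect on power to be estimated, so this adds no separate finding.

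None of these replies reconciles 16 recruits and 25% attrition with a minimum of 13 completers.

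**Conclusion.** The point holds in a limited form. By the article's own figures, 12 completers are expected where it says at least 13 are needed. Taking SD 10 as the SD of the paired differences, power at 12 is 75.9% for a one-sided test and 64.2% for a two-sided test at α = .01, so the stated 80% is not delivered on either reading. The one-sided shortfall is modest, about 4 percentage points; the two-sided one is about 16. Which applies cannot be settled from the article, because sidedness is not given. If the SD is that of single values, the size of the shortfall depends on an unstated correlation, and at a high correlation power at 12 would exceed 80%.

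**What to change.** 1. State whether the Group C paired *t* tests are one-sided or two-sided at α = .01, and whether the SD of 10 is that of paired differences or of single values (with the assumed correlation, if the latter).
2. Restate the power at the expected 12 evaluable patients: about 76% if one-sided, about 64% if two-sided, under the paired-difference SD.
3. Say that a nonsignificant Group C result will be interpreted with that power in mind.

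This is wording only and needs no further patients. If the sponsor prefers to keep 80% power, the target consistent with 25% attrition is 18 recruits for a one-sided test or 22 for a two-sided one, that is 2 or 6 more than planned.

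One option, not a required correction, is a single prespecified contrast of nociceptive minus nonnociceptive values at two-sided α = .05. It would have 88.3% power at 12 completers if d = 1 carries over to it. The price is a different estimand: the planned comparison for each nociceptive procedure would become secondary.

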**Methods:**

The NOL will be monitored in three ICU patient groups: (1) Group A, participants able to self-report their pain (the reference standard criterion using the 0-10 Faces Pain Thermometer) and express behaviors; (2) Group B, participants unable to self-report but able to express behaviors (the alternative standard criterion using the Critical-Care Pain Observation Tool); and (3) Group C, participants unable to self-report and express behaviors. The NOL will be tested before, during, and after two types of standard care procedures: (1) nonnociceptive (eg, cuff inflation to measure blood pressure, soft touch) and (2) nociceptive (eg, tube or drain removal, endotracheal or tracheal suctioning). Receiver operating characteristic curve analysis of the NOL will be performed for Groups A and B using pain standard measures as reference criteria. Mixed linear models for repeated measures will be used to compare time points, procedures, and their interaction in each group (A, B, and C). Based on power analyses and considering an attrition rate of 25%, a total sample size of 146 patients (68 in Group A, 62 in Group B, and 16 in Group C) is targeted.

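### The recruitment targets allow for 25% attrition by multiplying by 1.25 instead of dividing by 0.75, so they leave slightly fewer evaluable patients than the plan requires in all three groups

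*Protocol article*

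**What the plan says.** The Sample Size Calculation section of the protocol article first fixes the numbers needed for analysis. For the primary ROC analysis it works "considering a clinically acceptable AUC of 0.75" ("using a null hypothesis of AUC=0.50") "with a power of 80% and an adjusted α of .025". For Group A, "using a ratio of 2:1 in pain:no pain cases", it concludes that "a sample of 54 patients is required". Group B needs 50, at a pain to no-pain ratio of 1.5:1. Group C needs at least 13, for paired t tests of a mean NOL increase of 10 with SD 10, at 80% power and α .01.

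The section then allows for loss: "Considering an attrition rate of 25% (data collection was completed in 73% of consenting patients in our pilot work"). From this it derives that "recruitment targets include 68 patients in Group A, 62 patients in Group B, and 16 in Group C", 146 in total. The Methods paragraph of the Abstract repeats the result: "considering an attrition rate of 25%, a total sample size of 146 patients".

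**The concern.** The attrition rate is a proportion of those recruited. The section's own evidence uses that base, because the 73% pilot completion is counted among patients who consented. If a quarter of recruits are lost, three quarters remain, so the target must be the required number divided by 0.75. Adding a quarter to the required number gives less than that.

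The three required sizes, the attrition rate and the three targets therefore cannot all be right together. At stake is whether 146 recruits deliver the 54, 50 and 13 evaluable patients, and the 80% power, that the plan attaches to them.

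**Working it through.** **Inputs, all from the Sample Size Calculation section.** Required sizes 54 / 50 / 13; attrition 25%; pilot completion 73%; targets 68 / 62 / 16; AUC 0.75 against 0.50, α .025, ratios 2:1 and 1.5:1; Group C mean difference 10, SD 10, α .01.

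**1. Reproducing the stated targets.** Required size × 1.25:
- A: 54 × 1.25 = 67.5, stated as 68
- B: 50 × 1.25 = 62.5, stated as 62
- C: 13 × 1.25 = 16.25, stated as 16

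The sum is 68 + 62 + 16 = 146, as published. A is rounded up, B and C down.

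**2. What the targets yield, and what 25% attrition calls for.**

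| Group | Required | Target | Evaluable at 25% loss (target × 0.75) | Largest loss tolerated (1 − required/target) | Required/0.75, rounded up |
|---|---|---|---|---|---|
| A | 54 | 68 | 51 | 20.6% | 72 |
| B | 50 | 62 | 46.5 | 19.4% | 67 |
| C | 13 | 16 | 12 | 18.8% | 18 |

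The last column sums to 157, which is 11 more than 146. Rounding explains little of this: targets of 63 and 17 in B and C would still leave 47.25 and 12.75.

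As a sensitivity check at the pilot's 73% completion, the stated targets leave 49.6, 45.3 and 11.7. Dividing by 0.73 and rounding up gives 74 + 69 + 18 = 161.

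**3. Power in Groups A and B.** The plan's software is not available to us, so this is a normal approximation. With n1 pain and n0 no-pain cases:
- null SE: s0 = √[(n1 + n0 + 1)/(12·n1·n0)]
- SE at AUC 0.75 (Hanley-McNeil): s1 = √{[0.75·0.25 + (n1 − 1)(q1 − 0.75²) + (n0 − 1)(q2 − 0.75²)]/(n1·n0)}, with q1 = 0.75/1.25 = 0.600 and q2 = 2·0.75²/1.75 = 0.643
- power = Φ[(0.25 − 2.241·s0)/s1], where 2.241 is the two-sided .025 critical value

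This needs 52 (A) and 49 (B) for 80% power, within two patients of the plan's 54 and 50, so it is a fair stand-in.

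| Group | n (n1 : n0) | s0 | s1 | Power |
|---|---|---|---|---|
| A, required | 54 (36 : 18) | 0.0841 | 0.0665 | 82% |
| A, expected | 51 (34 : 17) | 0.0866 | 0.0685 | 79% |
| B, required | 50 (30 : 20) | 0.0842 | 0.0683 | 82% |
| B, expected | 46.5 (27.9 : 18.6) | 0.0873 | 0.0709 | 78% |

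**4. Power in Group C.** Paired t test by the noncentral t distribution, taking the SD of 10 as that of the paired difference, so the effect size is 10/10 = 1 and the noncentrality is √n. The plan does not state whether the test is one- or two-sided.
- One-sided .01: 13 is the smallest size reaching 80%, so this reproduces the plan. Power is 81% at 13 and 76% at 12.
- Two-sided .01: 16 would be needed. Power is 70% at 13 and 64% at 12.

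**The case against.** The strongest reply is that the loss is small. By the approximation above, 54 and 50 carry a margin over the 52 and 49 needed, so against 80% power the expected shortfall is about 1 patient in A and 2.5 in B. Group C loses one patient. No analysis or design feature changes. This stands and sets the weight of the point, but it does not make the published figures agree.

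A second reply is that losses may be lower than in the pilot studies. The section on limitations says these arose mainly from missed procedures, that only two nociceptive procedures were eligible then, and that a wider choice may help. If loss stayed near 19%, the targets would suffice. But the same section accepts that some procedures may still be missed, and the plan kept 25% as its planning rate.

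A third is that the mixed model tolerates missing data. That concerns the repeated-measures comparison. The sizes were set for ROC curves and paired t tests, which need the procedure to be observed.

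Two stronger readings are tempting. A reader might infer that attrition leaves Group C with 64% power. That figure assumes a two-sided test, under which 13 patients never gave 80%; most of the gap is a separate question of sidedness. A reader might also infer that 161 is the correct total. The plan adopts 25% and cites the 73% in support, so 161 is a sensitivity figure only.

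**Conclusion.** The targets are wrong as written; the consequence is minor to moderate. At the plan's own 25% attrition, 68 / 62 / 16 leave about 51 / 46.5 / 12 evaluable patients against 54 / 50 / 13, and nothing elsewhere in the article repairs this. The counts are plain arithmetic and rest only on attrition being a proportion of recruits, as the pilot figure is.

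The cost is about 3 points of power in Group A, 4 in Group B and 5 in Group C. These sizes are approximate: they assume two-sided .025 for the ROC tests, one-sided .01 for Group C, and the plan's own case ratios and effect sizes. The documents do not support a claim that the study is seriously underpowered or must recruit more patients.

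**What to change.** Correct the statement in the Sample Size Calculation section and in the Abstract, in one of two ways that leave recruitment at 146:
- give the expected evaluable numbers at 25% attrition (about 51 / 46 / 12) and the resulting power, recomputed in the plan's own software with sidedness stated; or
- say that the targets cover attrition of only about 19%.

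Either takes a sentence and no extra patients. Alternatively, adopt the targets that do match 25% attrition, 72 / 67 / 18 = 157. That means 11 more patients and an amendment, and is optional. If the sponsor wants to show sensitivity to the pilot's 73% completion, the figures are 74 / 69 / 18 = 161, labelled as such.
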